#### 6. QUESTIONS FOR MEDICAL STORES LIMITED STAFF

|     |                                                                                                                                   |  |
|-----|-----------------------------------------------------------------------------------------------------------------------------------|--|
| 6.1 | What do you see as the main challenges in providing health facilities with the ART supplies that they request in a timely manner? |  |
|-----|-----------------------------------------------------------------------------------------------------------------------------------|--|

|     |                                                                                                                 |  |
|-----|-----------------------------------------------------------------------------------------------------------------|--|
| 6.2 | What parts or aspects of the ART supply chain that work well?                                                   |  |
| 6.3 | What do you think is a way to improve the supply system for ART drugs?                                          |  |
| 6.4 | What portion of stable ART patients in Lusaka do you think are getting 3-month prescriptions now?               |  |
| 6.5 | Do you think it is a good thing to provide most stable patients with multi-month prescriptions? Why or why not? |  |
| 6.6 | What do you think are the main challenges or issues with providing patients with 3-month refills?               |  |
| 6.7 | What kinds of changes do you think would be needed to provide more patients with 3 month refills?               |  |

## Patient Exit Interview

### 1 PRELIMINARY INFORMATION

|     |                |   |   |  |   |   |   |   |   |   |   |   |
|-----|----------------|---|---|--|---|---|---|---|---|---|---|---|
| 1.1 | Interview date |   |   |  | / |   |   | / |   |   |   |   |
|     |                | D | D |  |   | M | M |   | Y | Y | Y | Y |

|                        |  |
|------------------------|--|
| HEALTH FACILITY |  |
| Name of facility       |  |

|                                        |            |      |   |   |   |           |          |   |   |   |   |   |
|----------------------------------------|------------|------|---|---|---|-----------|----------|---|---|---|---|---|
| VERIFICATION                    |            |      |   |   |   |           |          |   |   |   |   |   |
| 1.1                                    | Start time |      |   | : |   |           | End time |   |   | : |   |   |
|                                        |            | H    | H |   | M | M         |          | H | H |   | M | M |
| Survey is complete and accurate |            | Name |   |   |   | Signature |          |   |   |   |   |   |
| 1.2                                    | Enumerator |      |   |   |   |           |          |   |   |   |   |   |
| 1.3                                    | Supervisor |      |   |   |   |           |          |   |   |   |   |   |

|                            |                                                                                                                        |     |  |   |                      |
|----------------------------|------------------------------------------------------------------------------------------------------------------------|-----|--|---|----------------------|
| SCREENING QUESTIONS |                                                                                                                        |     |  |   |                      |
| 1.4                        | Is the patient under 18 years old?                                                                                     | No  |  | 1 | END           |
|                            |                                                                                                                        | Yes |  | 2 |                      |
| 1.5                        | Have you confirmed with the Pharmacist that the patient is on first line treatment?                                    | No  |  | 1 | END           |
|                            |                                                                                                                        | Yes |  | 2 |                      |
| 1.6                        | After reading the consent form.
Has the patient clearly read the consent form and provided informed consent? | No  |  | 1 | END           |
|                            |                                                                                                                        | Yes |  | 2 |                      |
| 1.7                        | After reading the consent form.
Has the participant agreed to have the conversation recorded?                | No  |  | 1 | DO NOT RECORD |
|                            |                                                                                                                        | Yes |  | 2 |                      |

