## *6.2 Eligibility for recruitment*

### 6.1.4 Inclusion criteria

Facilities that have agreed to participate and have the potential to increase the proportion of stable patients on 3-month refills by 20% (currently have less than 80% of stable patients on 3 month refills).

Adult ART patients aged 18 years and over will be eligible for the exit interview.

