### 6.5.1 Secondary analyses

Secondary analyses will consider the impact of the intervention by comparing mean and the variability of patient wait times and score of satisfaction between the intervention and control sites. We will run similar bivariable comparisons to examine how these factors may be associated with potential confounders. Then, paired t-tests will be used to examine the mean differences between the two groups for the variable of patient wait times and other secondary outcomes. Conditional multivariable analyses will be used to account for matched analyses as well as potential confounders. In addition, we will

describe compliance to the intervention and qualitative assessment on process successes and failures as well as patient and staff satisfaction.

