## ART Register Data Collection Form

### VERIFICATION AND FACILITY INFORMATION

|                                      |             |                  |                          |
|--------------------------------------|-------------|------------------|--------------------------|
| Data is complete and accurate | Name | Signature | Date (dd/mm/yyyy) |
| 2.1 Enumerator                |             |                  | / / 2014                 |
| 2.2 Supervisor                |             |                  | / / 2014                 |
| 2.3 Name of facility          |             |                  |                          |

ELIGIBILITY: ALL PATIENTS ON 1ST LINE TREATMENT, 18YEARS OLD OR OVER WHO MADE AT LEAST ONE APPOINTMENT DURING THE PREVIOUS 3 MONTHS

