| 4.6 | Are there any reasons why it is good to receive 3 months of ART drugs at a time?

Choose all that apply (Do not prompt or mention options – allow the respondent to answer directly) | Not having to come back to clinic as often                                                                |  | 1  |  |
|     |                                                                                                                                                                                                   | Knowing that I have the medication I need for at least 3 months                                           |  | 2  |  |
|     |                                                                                                                                                                                                   | Not having to wait in line as long at the pharmacy because there are not as many patients coming each day |  | 3  |  |
|     |                                                                                                                                                                                                   | Other (specify):
_____                                                                                 |  | 98 |  |
|     |                                                                                                                                                                                                   | Don't know                                                                                                |  | 99 |  |

**QUESTIONS TO BE USED IN ENDLINE, POST-INTERVENTION SURVEY ONLY, ONLY FOR THOSE PATIENTS IN FACILITIES THAT RECEIVED AN INTERVENTION (IN ADDITION TO ABOVE)**

|     |                                                                                                       |            |  |    |             |
|-----|-------------------------------------------------------------------------------------------------------|------------|--|----|-------------|
| 4.7 | Have there been any changes in the care that you have received at this facility in the last 4 months? | No         |  | 0  | SKIP TO 4.6 |
|     |                                                                                                       | Yes        |  | 1  |             |

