|     |                                                                                                       | Don't know |  | 99 | SKIP TO 4.6 |
| 4.8 | Please describe any changes that have happened in the care that you receive?                          |            |  |    |             |
| 4.9 | Did you receive ART drugs during this                                                                 | No         |  | 0  | SKIP        |

|      |                                                                                                                                              |                        |  |    |              |
|------|----------------------------------------------------------------------------------------------------------------------------------------------|------------------------|--|----|--------------|
|      | visit?                                                                                                                                       |                        |  |    | TO 4.8       |
|      |                                                                                                                                              | Yes                    |  | 1  |              |
|      |                                                                                                                                              | Don't know             |  | 99 | SKIP TO 4.8  |
| 4.10 | How many months of ART drugs did you receive?                                                                                                | Less than one month    |  | 0  | SKIP TO 4.10 |
|      |                                                                                                                                              | One month              |  | 1  |              |
|      |                                                                                                                                              | Two months             |  | 2  |              |
|      |                                                                                                                                              | Three months           |  | 3  |              |
|      |                                                                                                                                              | More than three months |  | 4  |              |

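### The age screener in the patient exit interview (Annex 7, item 1.4) is inverted as printed: it ends the interview for adults and passes minors; separately, six endline skips in the same form do not lead forward

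*Combined protocol and SAP*

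**What the plan says.** Section 6.1.4 of the protocol sets the age rule for the exit interview: "Adult ART patients aged 18 years and over will be eligible for the exit interview".

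The screening block of the Patient Exit Interview (Annex 7) applies that rule through item 1.4: "Is the patient under 18 years old". The No row (code 1) carries END. The Yes row (code 2) carries no instruction, so the interview goes on. The next item, 1.5, has the same layout: "Have you confirmed with the Pharmacist that the patient is on first line treatment", again with END on No. Item 1.6, on consent, is laid out likewise.

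Later in the form, the block starting at item 4.7 is for the endline survey only and is restricted by its own banner: "ONLY FOR THOSE PATIENTS IN FACILITIES THAT RECEIVED AN INTERVENTION (IN ADDITION TO ABOVE". Three of its items carry skips:

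- Item 4.7, "Have there been any changes in the care that you have received at this facility in the last 4 months", sends No and Don't know to 4.6.
- Item 4.9, on whether ART drugs were received at the visit, sends No and Don't know to 4.8.
- Item 4.10, "How many months of ART drugs did you receive", sends Less than one month and Don't know to 4.10.

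**The concern.** Item 1.4 is not background text. It is the rule by which an enumerator or a tablet decides who is interviewed, and it says the reverse of section 6.1.4. Section 7.2 allows direct entry on tablets, where a skip built from this form would be enforced without anyone weighing whether it made sense.

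The exit interview is the study's source for what patients report. Satisfaction and perceived quality of care, experience of moving to multi-month refills, and patients' view of supply reliability are all listed as secondary outcomes. Section 6.5.1 plans to compare the "score of satisfaction between the intervention and control sites". Item 4.1, the form's only rated satisfaction item, lies behind the screener. Admitting minors would also breach the study's own eligibility rule.

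The skip faults matter less, but they fall on the items meant to describe how patients in intervention clinics experienced the change.

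**Working it through.** No arithmetic bears on the main point. The check is to trace each printed answer and compare the result with the protocol text.

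**1. The age screener**

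| Patient | Answer to item 1.4 | Printed instruction | Form's result | Section 6.1.4 |
|---|---|---|---|---|
| 18 or over | No | END | Not interviewed | Eligible |
| Under 18 | Yes | none | Continues to 1.5 | Not eligible |

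Both rows contradict the protocol. Items 1.5 and 1.6 also end on No, and there it is right, because each asks whether a requirement has been met. Item 1.4 has the same routing under a question phrased the other way round. An error in reading the PDF is unlikely, since END stands on the No row and the Yes row has its own empty cell, as in the neighbouring items. The source page can confirm this.

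**2. Reach of the screener fault**

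- It stands at the front of the exit interview, so it applies to every such interview at all 16 clinics, at baseline and endline.
- The primary outcome does not pass through it. Section 6.3.1 obtains the baseline proportion by linking the ART register to pharmacy dispensing data, and both register forms (Annexes 1 and 4) state the age limit the right way round: "18YEARS OLD OR OVER WHO MADE AT LEAST ONE APPOINTMENT DURING THE PREVIOUS 3 MONTHS".

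**3. The skips**

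| Item | Answers that skip | Printed target | Direction |
|---|---|---|---|
| 3.3 | No, Don't know | 3.5 | forward |
| 3.5 | No, Don't know | 3.8 | forward |
| 4.7 | No, Don't know | 4.6 | backward |
| 4.9 | No, Don't know | 4.8 | backward |
| 4.10 | Less than one month, Don't know | 4.10 | to itself |

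Section 3 of the form has 2 + 2 = 4 skip instructions, all sound. Section 4 has 2 + 2 + 2 = 6: four point backwards, two point to their own item, none points forward. Followed literally with an unchanged answer, each of the six repeats and the remaining items up to 4.14 are never reached.

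**4. Reach of the skip faults**

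The banner limits the block to endline patients in facilities that received the intervention. Section 6.1 assigns one facility of each pair, so that is 16 / 2 = 8 clinics in one round. Item 4.1 is asked before the block, and control clinics are not asked the block at all. The skip faults therefore cannot affect the between-arm satisfaction comparison.

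**The case against.** The best case against giving this weight is that it is a clerical slip in an annex and that the intent is plain. Section 6.1.4 and both register forms say adults; nobody chose to interview minors. The slip arose, most likely, because a negatively phrased question was put into a template in which No ends the interview. There are also safeguards: enumerator and supervisor sign each form, age is recorded at item 2.1, section 6.3.4 provides a screening log, and section 7.3 provides consistency and range checks. On paper, a trained interviewer would probably work around item 1.4 and would not repeat an answered question.

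Most of this stands as a limit on the likely damage. A reader might infer that the satisfaction and experience outcomes would have no valid data at all. The documents do not support that as a forecast: it needs the form to be followed or programmed literally, everywhere and in both rounds, without anyone noticing. What does not stand is the suggestion that the form can be left alone. The section 7.3 checks come after a component is completed; they might expose minors who were interviewed, but they cannot recover adults already turned away. An instrument should not rely on staff disregarding it.

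A reader might also infer that every section 4 target is simply three too low, because adding three gives forward targets (4.6 to 4.9, 4.8 to 4.11, 4.10 to 4.13). Stale numbering is a plausible cause, but the documents give no other numbering to check against. For item 4.10 the rule gives a doubtful result. It would carry patients past 4.11, on ever having received three or more months of drugs, and 4.12, on adherence advice, with no stated reason, while patients who received no drugs at all would be asked both.

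**Conclusion.** The screener is wrong as written and contradicts section 6.1.4. It should be corrected before fieldwork. Its reach is every exit interview and the patient-reported secondary outcomes that depend on them; the register-based primary outcome is not affected. How much data would actually be lost depends on whether the form is applied literally, which the documents cannot settle. The risk is greatest if the routing is programmed on tablets.

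The six section 4 skips are also wrong as printed, but this is a lesser correction. It concerns descriptive endline items in the 8 intervention facilities and leaves the satisfaction comparison intact. The documents show that the targets are wrong; they do not show what all the right targets are.

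Both conclusions assume that the printed form matches the extracted table.

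**What to change.** 1. In Annex 7, item 1.4, either move END to the Yes row or ask whether the patient is 18 or older and keep END on No. The second option matches the pattern of items 1.5 and 1.6.
2. Have the sponsor confirm the intended forward target for each skip at 4.7, 4.9 and 4.10, including the Don't know rows, and correct them. Do not apply a uniform shift in numbering without that check, above all at 4.10.
3. Before fieldwork, run each possible answer through the paper form and any tablet version, with at least one adult and one under-18 test case at the screener.

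The cost is a corrected form, a notification to the ethics board (section 6.3.4 refers to questionnaires that it has approved) and a short routing test. Design, sample size and analysis are unchanged.

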## 2 PATIENT INFORMATION

| DEMOGRAPHICS OF PATIENT |                                                                  |                                  |  |    |
|-------------------------|------------------------------------------------------------------|----------------------------------|--|----|
| 2.1                     | Age                                                              |                                  |  |    |
| 2.2                     | How long does it take you to get from your home to the facility? |                                  |  |    |
| 2.3                     | Unit of time                                                     | Minutes                          |  | 1  |
|                         |                                                                  | Hours                            |  | 2  |
| 2.4                     | What mode of transportation do you use to get to the facility?   | Walking                          |  | 1  |
|                         |                                                                  | Biking                           |  | 2  |
|                         |                                                                  | Minibus                          |  | 3  |
|                         |                                                                  | Personal Car                     |  | 4  |
|                         |                                                                  | Other, specify: _____            |  | 98 |
| 2.5                     | Sex                                                              | Male                             |  | 1  |
|                         |                                                                  | Female                           |  | 2  |
| 2.6                     | What is your marital status?                                     | Single, never married            |  | 0  |
|                         |                                                                  | Married, monogamous              |  | 1  |
|                         |                                                                  | Married, polygamous              |  | 2  |
|                         |                                                                  | Not married, living with partner |  | 3  |
|                         |                                                                  | Widowed                          |  | 4  |
|                         |                                                                  | Divorced/separated               |  | 5  |
|                         |                                                                  | Other, specify: _____            |  | 98 |
|                         |                                                                  | Don't know                       |  | 99 |
| 2.7                     | What is the highest level of education you have completed?       | No formal education              |  | 0  |
|                         |                                                                  | 1                                |  | 1  |
|                         |                                                                  | 2                                |  | 2  |
|                         |                                                                  | 3                                |  | 3  |
|                         |                                                                  | 4                                |  | 4  |
|                         |                                                                  | 5                                |  | 5  |
|                         |                                                                  | 6                                |  | 6  |
|                         |                                                                  | 7                                |  | 7  |
|                         |                                                                  | 8                                |  | 8  |
|                         |                                                                  | 9                                |  | 9  |
|                         |                                                                  | 10                               |  | 10 |
|                         |                                                                  | 11                               |  | 11 |
|                         |                                                                  | 12                               |  | 12 |
|                         |                                                                  | Certificate program              |  | 14 |
|                         |                                                                  | Other, specify: _____            |  | 98 |
|                         |                                                                  | Don't know                       |  | 99 |
|                         |                                                                  |                                  |  |    |

| 3. ART ADHERENCE AND BARRIERS TO CARE |                                                                                                                                                                                      |                                      |  |      |  |    |             |
|---------------------------------------|--------------------------------------------------------------------------------------------------------------------------------------------------------------------------------------|--------------------------------------|--|------|--|----|-------------|
| 3.1                                   | When were you first diagnosed with HIV?
Prompt: Year of diagnosis                                                                                                          | Year                                 |  |      |  |    |             |
| 3.2                                   | When did you first start receiving care at this ART clinic? ( Month and year )                                                                                                | Month                                |  | Year |  |    |             |
| 3.3                                   | In the past month, have you missed any doses of ARV pills?                                                                                                                           | No                                   |  |      |  | 0  | SKIP TO 3.5 |
|                                       |                                                                                                                                                                                      | Yes                                  |  |      |  | 1  |             |
|                                       |                                                                                                                                                                                      | Don't know                           |  |      |  | 99 | SKIP TO 3.5 |
| 3.4                                   | Why did you miss those doses?

Choose all that apply, ranking those in order of importance (Do not prompt or mention options – allow the respondent to answer directly) | Side effects                         |  |      |  | 1  |             |
|                                       |                                                                                                                                                                                      | Shared pills with others             |  |      |  | 2  |             |
|                                       |                                                                                                                                                                                      | Forgot                               |  |      |  | 3  |             |
|                                       |                                                                                                                                                                                      | Felt better                          |  |      |  | 4  |             |
|                                       |                                                                                                                                                                                      | Too ill                              |  |      |  | 5  |             |
|                                       |                                                                                                                                                                                      | Stigma, disclosure or privacy issues |  |      |  | 6  |             |
|                                       |                                                                                                                                                                                      | Drug stockout                        |  |      |  | 7  |             |
|                                       |                                                                                                                                                                                      | Lost or ran out of pills             |  |      |  | 8  |             |
|                                       |                                                                                                                                                                                      | Delivery or travel problems          |  |      |  | 9  |             |
|                                       |                                                                                                                                                                                      | Alcohol                              |  |      |  | 11 |             |
|                                       |                                                                                                                                                                                      | Depression                           |  |      |  | 12 |             |
|                                       |                                                                                                                                                                                      | Pill burden                          |  |      |  | 13 |             |
|                                       |                                                                                                                                                                                      | Lack of food                         |  |      |  | 14 |             |
|                                       |                                                                                                                                                                                      | Other (specify):
_____            |  |      |  | 98 |             |
| 3.5                                   | Thinking back on the previous 3 months, have you missed any scheduled appointments?                                                                                                  | No                                   |  |      |  | 0  | SKIP TO 3.8 |
|                                       |                                                                                                                                                                                      | Yes                                  |  |      |  | 1  |             |
|                                       |                                                                                                                                                                                      | Don't know                           |  |      |  | 99 | SKIP TO 3.8 |
| 3.6                                   | If so, how many appointments did you miss?

Input number, or 99 for don't know                                                                                          |                                      |  |      |  |    |             |
| 3.7                                   | If so, why?

Choose all that apply (do not prompt or mention choices – allow the respondent to answer directly)                                                         | Forgot                               |  |      |  | 1  |             |
|                                       |                                                                                                                                                                                      | Felt better                          |  |      |  | 2  |             |
|                                       |                                                                                                                                                                                      | Stigma/disclosure                    |  |      |  | 3  |             |
|                                       |                                                                                                                                                                                      | Too ill                              |  |      |  | 4  |             |
|                                       |                                                                                                                                                                                      | Lack of money                        |  |      |  | 5  |             |

|                    |                                                                                                                                                             |                                                        |  |    |  |
|--------------------|-------------------------------------------------------------------------------------------------------------------------------------------------------------|--------------------------------------------------------|--|----|--|
|                    |                                                                                                                                                             | Couldn't get out of school or work                     |  | 6  |  |
|                    |                                                                                                                                                             | Disliked patient experience at the facility            |  | 7  |  |
|                    |                                                                                                                                                             | Facility was too far                                   |  | 8  |  |
|                    |                                                                                                                                                             | Didn't have money for transport                        |  | 9  |  |
|                    |                                                                                                                                                             | Went to a different facility                           |  | 10 |  |
|                    |                                                                                                                                                             | Other (specify): _____                                 |  | 98 |  |
|                    |                                                                                                                                                             | Don't know                                             |  | 99 |  |
| 3.8                | What are the main difficulties that you face in receiving care at this clinic?                                                                              | Transportation/distance to facility                    |  | 1  |  |
|                    |                                                                                                                                                             | Taking time off from school/work to go to facility     |  | 2  |  |
|                    |                                                                                                                                                             | Waiting times at facility                              |  | 3  |  |
|                    |                                                                                                                                                             | Stigma/disclosure issues                               |  | 4  |  |
|                    |                                                                                                                                                             | Side effects of medication                             |  | 7  |  |
|                    |                                                                                                                                                             | Short refill period                                    |  | 8  |  |
|                    |                                                                                                                                                             | Other (specify): _____                                 |  | 98 |  |
|                    |                                                                                                                                                             | Don't know                                             |  | 99 |  |
| 4. ART CARE |                                                                                                                                                             |                                                        |  |    |  |
| 4.1                | On a scale of 1 to 5, 1 being very unhappy and 5 being very happy, how happy are you with how the health workers at the facility interacted with you today? | Very unhappy                                           |  | 1  |  |
|                    |                                                                                                                                                             | Somewhat unhappy                                       |  | 2  |  |
|                    |                                                                                                                                                             | Neutral                                                |  | 3  |  |
